## Abstract

**Introduction:**

Heart failure with preserved ejection fraction (HFpEF) is a highly complex clinical syndrome associated with significant morbidity and mortality. Its underlying mechanisms are poorly understood, treatment options are limited, the disease burden on patients is substantial, and clinical outcomes are poor. Previous clinical studies have preliminarily suggested that Shengxian Yixin Granule (SXYX) is an effective herbal formula for the treatment of HFpEF, but it lacks high-quality clinical evidence. This study therefore plans to conduct a randomized controlled trial (RCT) to evaluate the efficacy and safety of SXYX in treating HFpEF, aiming to provide a new therapeutic strategy for this condition.

**Methods:**

This study is a multicenter, randomized, double-blind, placebo-controlled clinical trial. It will be conducted at four Chinese medicine hospitals in China. A total of 148 eligible patients with HFpEF will be enrolled and randomly assigned in a 1:1 ratio to the SXYX group or the placebo group. The SXYX group will receive Shengxian Yixin Granule, while the placebo group will receive a matching placebo. Both groups will receive standard Western medical therapy as background treatment. The treatment duration for all groups is 24 weeks. The primary outcome is the change in peak VO_2_ (assessed by cardiopulmonary exercise testing) from baseline to 24 weeks. Secondary outcome measures include the change in peak oxygen uptake from baseline to 12 weeks, NT-proBNP, echocardiographic parameters, NYHA functional class, 6-minute walk test distance (6MWT), Traditional Chinese Medicine (TCM) syndrome scale, major symptoms and signs, EQ-5D score, and coagulation function. These outcomes will be used to evaluate the efficacy of SXYX. Routine blood, urine, and stool tests, liver and kidney function tests, electrocardiograms, and adverse events will be used to assess the safety of SXYX. Wearable monitoring devices will be used for out-of-hospital, dynamic, and multidimensional assessment of patients’ exercise tolerance, including heart rate, blood oxygen saturation, step count, and walking distance.

**Discussion:**

This study will evaluate the efficacy and safety of SXYX in treating HFpEF. The findings will provide a scientific basis for the clinical application of SXYX.

**Clinical Trial Registration:**

https://itmctr.ccebtcm.org.cn, identifier ITMCTR2026000833.

## Introduction

1

Heart failure affects more than 64 million people worldwide. With population aging and improvements in post-myocardial infarction treatment and survival rates, its prevalence continues to rise. Among the various subtypes, the prevalence of HFpEF has increased significantly in recent years (1, 2). HFpEF is a complex clinical syndrome characterized by a left ventricular ejection fraction (LVEF) ≥50%, along with symptoms such as dyspnea and reduced exercise tolerance. HFpEF accounts for approximately 50% of all heart failure cases and has become the predominant form of heart failure worldwide (3, 4). HFpEF is associated with substantial morbidity and mortality, with a 30-day readmission rate of approximately 20%. In-hospital, 1-year, and 5-year mortality rates range from 2.4% to 4.9%, 20% to 29%, and 53% to 74% (5, 6). Landmark studies in the treatment of HFpEF include the EMPEROR-Preserved and DELIVER trials, which demonstrated that SGLT2 inhibitors reduced the composite endpoint of cardiovascular death or hospitalization for heart failure (7, 8). However, the absolute risk reduction for the primary composite endpoint in these trials was approximately 3%, and this benefit was largely driven by a reduction in heart failure hospitalizations or urgent visits, rather than a decrease in cardiovascular mortality (9). STEP-HFpEF and STEP-HFpEF DM trials demonstrated that in patients with HFpEF and comorbid obesity (with or without type 2 diabetes), treatment with the GLP-1 receptor agonist semaglutide significantly improved heart failure-related symptoms, enhanced exercise tolerance, and substantially reduced body weight (10, 11). The SUMMIT trial further showed that in patients with HFpEF and obesity, the GIP/GLP-1 dual receptor agonist tirzepatide reduced the risk of the composite endpoint of cardiovascular death or worsening heart failure and improved health status (12). However, these benefits were observed only in HFpEF patients with comorbid obesity. In the PARAGON-HF trial, sacubitril/valsartan did not achieve a statistically significant reduction in the primary composite endpoint of total heart failure hospitalizations and cardiovascular death among the overall HFpEF population (13). Despite significant advances in the prevention and management of HFpEF in modern medicine, patients’ treatment needs remain unmet.

Traditional Chinese Medicine (TCM) has been used for thousands of years and is widely applied in clinical practice for the treatment of acute and chronic heart failure, which has shown promising but preliminary evidence of efficacy, although the existing studies are limited by heterogeneity in study design, patient populations, and TCM formulations. TCM treatment for HFpEF has been shown to significantly improve clinical symptoms, enhance quality of life, and increase exercise tolerance, as well as to reduce fluid retention, ameliorate cardiac remodeling, and improve cardiac function (14, 15). Multiple meta-analyses of RCTs have shown that integrated traditional Chinese and Western medicine therapy improves quality of life and exercise tolerance in HFpEF patients and has a favorable safety profile (16, 17). According to the *2025 Expert Consensus on the Integrated Traditional Chinese and Western Medicine Diagnosis and Treatment of Heart Failure with Preserved Ejection Fraction* (18), the main TCM syndrome patterns of HFpEF include Qi deficiency with blood stasis, Qi-Yin deficiency with blood stasis, and Yang deficiency with blood stasis and fluid retention, among which Qi deficiency with blood stasis is the most common type in clinical practice. Such patients present with Qi deficiency manifestations, including fatigue, reluctance to speak, easy fatigability upon exertion, spontaneous sweating, and a low, weak voice, as well as blood stasis manifestations, such as a purplish-dark complexion, lips, or nails, and a pale-dark tongue with petechiae or ecchymoses.

Our team developed SXYX based on the core pathogenesis of Qi deficiency with blood stasis in HFpEF patients, following the therapeutic principle of supplementing Qi and elevating sunken Qi, as well as activating blood circulation and resolving stasis. SXYX is widely used for the treatment of HFpEF patients at The First Affiliated Hospital of Henan University of Chinese Medicine as a hospital-approved formula that can be prescribed at any time (Yu Pharmaceutical Preparation Approval No. Z20250008000, where “Yu” is the official abbreviation for Henan Province). It has also been granted a China Invention Patent (Patent No. ZL202310555277.X). SXYX consists of 13 herbal medicines (see Table 1). Preliminary clinical studies have shown that SXYX is safe and effective for treating HFpEF; however, these earlier studies had limitations, including a lack of scientific rigor in study design and an insufficient sample size. Therefore, the present study was designed as a multicentre, randomised, double-blind, placebo-controlled clinical trial, incorporating data from wearable monitoring devices. The study aims to systematically evaluate the clinical efficacy and safety of SXYX in treating HFpEF, and to provide a scientific basis for the clinical application of SXYX.

**Table 1 T1:** The composition of Shengxian Yixin Granule.

Chinese name	Latin name	Medicinal part used	Weight ratio
Huang Qi	Hedysarum Multijugum Maxim	Root	30
Dang Shen	Codonopsis Radix	Root	20
Zhi Mu	Anemarrhenae Rhizoma	Rhizome	10
Chai Hu	Radix Bupleuri	Root	6
Sheng Ma	Cimicifugae Rhizoma	Rhizome	6
E Zhu	Curcumae Rhizoma	Rhizome	15
Gui Zhi	Cinnamomi Ramulus	Tender Twig	9
Gua Lou	Trichosanthes Kirilowii Maxim	Fruit	20
Xie Bai	Allium Azureum Ledeb	Bulb	20
Ban Xia	Arum Ternatum Thunb.	Tuber	15
Chi Shao	Radix Paeoniae Rubra	Root	15
Ting Li Zi	Lepidii Semen Descurainiae Semen	Seed	15
Gan Cao	licorice	Root and Rhizome	12

The exact daily dosage of individual herbs is not disclosed due to proprietary protection. The composition is presented as weight ratios (relative proportions) based on the raw herb materials.

## Methods and analysis

2

### Study design

2.1

This study is a multicenter, randomized, double-blind, placebo-controlled, parallel-group clinical trial. The study protocol has been approved by the Ethics Committee of The First Affiliated Hospital of Henan University of Chinese Medicine (approval No. 2026HL-041-01). The trial was registered on 27 March 2026 with the International Traditional Medicine Clinical Trial Registry (ITMCTR) at https://itmctr.ccebtcm.org.cn (registration number: ITMCTR2026000833). The study protocol was developed in strict accordance with the SPIRIT 2025 guidelines (19). The results of this trial will be reported in accordance with the CONSORT 2025 statement (20). The study will be conducted at four TCM hospitals in China: The First Affiliated Hospital of Henan University of Chinese Medicine, Lushi County Hospital of Traditional Chinese Medicine, Fangcheng County Hospital of Traditional Chinese Medicine, and Mianchi County Hospital of Traditional Chinese Medicine. A total of 148 eligible patients with HFpEF meeting the inclusion and exclusion criteria will be enrolled in the study. After providing written informed consent, patients will be randomly assigned in a 1:1 ratio to receive either SXYX or placebo for 24 weeks of treatment. The trial flow diagram is shown in Figure 1.

**Figure 1 F1:**
[figure not shown]
Flow chart of the study design. HFpEF, heart failure with preserved ejection fraction; SXYX, Shengxian Yixin Granule.

### Sample size calculation

2.2

This study is a multicenter, randomized, double-blind, placebo-controlled trial. The primary outcome is a continuous variable. The allocation ratio between the SXYX group and the placebo group is 1:1. The sample size will be calculated using the formula for comparing two independent means. The formula is as follows:$$n_{1}=n_{2}=2{\left[\frac{(Z_{\alpha /2}+Z_{\beta })\sigma }{\delta }\right]}^{2}$$Based on preliminary data from a small-sample, exploratory pilot study, the peak oxygen consumption (VO_2_ peak) in patients with HFpEF after 6 months of treatment was 20.2 ± 4.8 mL/kg/min in those receiving Chinese herbal medicine, and 18.9 ± 4.2 mL/kg/min in those receiving standard conventional medical therapy. The standard deviations of 4.8 and 4.2 from the preliminary data were used solely to estimate the population standard deviation (*σ*). Based on the OptimEx-Clin Study (21), the latest prognostic studies of percentage of predicted peak VO_2_ in HFpEF (22), and the published results of traditional Chinese medicine for HFpEF with the Qi-deficiency and blood-stasis pattern (23), the minimal clinically important difference for sample size calculation was set at 2.7 mL/kg/min.$$\sigma^{2}=(S_{{}_{1}}^{2}+S_{2}^{2})/2=(4.8^{2}+4.2^{2})/2=20.34$$$$n_{1}=n_{2}=2{\left[\frac{(Z_{\alpha }+Z_{\beta })\sigma }{\delta }\right]}^{2}=2\left[\frac{{\left(1.96+1.282\right)}^{2}\times 20.34}{2.7^{2}}\right]\approx 59$$The calculation yielded approximately 59 patients per group. Accounting for an anticipated 20% dropout rate, the required sample size was adjusted to 74 patients per group, resulting in a total enrollment of 148 patients.

### Inclusion criteria

2.3

Aged 18–75 years, of any gender.Based on the 2024 *Lancet Seminar “Heart failure with preserved ejection fraction: everything the clinician needs to know”* (3) and the 2019 *European Heart Journal consensus recommendation “How to diagnose heart failure with preserved ejection fraction: the HFA-PEFF diagnostic algorithm: a consensus recommendation from the Heart Failure Association (HFA) of the European Society of Cardiology (ESC)”* (24), the diagnostic criteria for HFpEF were jointly established. The pre-specified diagnostic threshold was set at ≥5 points for the confirmation of HFpEF. All echocardiographic recordings from the different sub-centres were sent to the central research laboratory for unified review. The diagnostic flowchart is shown in Figure 2.Based on the *Guideline for Diagnosis and Treatment of Chronic Heart Failure in Traditional Chinese Medicine (2022)* (25) published in the Journal of Traditional Chinese Medicine in 2022, the diagnostic criteria for the “Qi deficiency and blood stasis pattern” of HFpEF were formulated. The primary symptoms include palpitations, wheezing, fatigue, and shortness of breath. The secondary symptoms are: (i) languidness, disinclination to speak, and easy fatigue with activity; (ii) spontaneous sweating without obvious cause during the day, aggravated after activity; (iii) dull purplish complexion; (iiii) dull purplish lips. For tongue and pulse: the tongue body is purplish (or with ecchymoses, petechiae, or tortuous and cyanotic sublingual collaterals), and the pulse is deep, thready, or feeble and forceless. A diagnosis can be made when two primary symptoms and two secondary symptoms are present, in combination with the tongue and pulse findings. The Traditional Chinese Medicine syndrome score scale is shown in the Table 2.Patients were required to meet the following clinical stability criteria: New York Heart Association (NYHA) functional class II–III; no hospitalisation for acute heart failure, no acute coronary syndrome, and no percutaneous coronary intervention (PCI) or coronary artery bypass grafting (CABG) within the preceding 4 weeks; resting systolic blood pressure maintained within the range of 100–160 mmHg; active myocardial ischaemia rigorously excluded by resting electrocardiography, stress testing, or coronary computed tomography angiography; and a respiratory exchange ratio (RER) of ≥1.10 confirmed on cardiopulmonary exercise testing. In addition, patients’ symptoms and standard conventional medical therapy were required to be stable for at least 2–4 weeks before enrolment.Patients who voluntarily provide written informed consent.

**Figure 2 F2:**
[figure not shown]
HFpEF diagnostic algorithm. AF, atrial fibrillation; E:e', early diastolic mitral inflow velocity to early diastolic mitral annulus velocity; HFA-PEFF, Heart Failure Association Pre-test assessment, Echocardiography and natriuretic peptide, Functional testing, Final aetiology; HFpEF, heart failure with preserved ejection fraction; NT-proBNP, N-terminal pro-B type natriuretic peptide; SR, sinus rhythm. Reproduced with permission from “HFpEF diagnostic algorithm” by Patricia Campbell, Frans H Rutten, Matthew MY Lee, Nathaniel M Hawkins and Mark C Petrie.

**Table 2 T2:** Traditional Chinese medicine syndrome score scale (Qi deficiency and blood stasis pattern).

Symptoms		Scoring criteria
Primary symptoms	Palpitations	□0: None of the above symptoms □1: During ordinary physical activity □2: After slight exertion □3: Often occurs at rest
	Wheezing	□0: None of the above symptoms □1: During ordinary physical activity □2: After slight exertion □3: Often occurs at rest
	Fatigue	□0: None of the above symptoms □1: During daily activities □2: During mild exertion □3: Occurs without activity
	Shortness of breath	□0: None of the above symptoms □1: During daily activities □2: During mild exertion □3: Occurs without activity
Secondary symptoms	Languidness and disinclination to speak	□0: None of the above symptoms □1: Spiritlessness, fatigue, or shortness of breath with disinclination to speak □2: Low and weak voice or weak cough □3: Lassitude and drowsiness
	Spontaneous sweating	□0: None of the above symptoms □1: Slight sweating after activity □2: Moist skin, aggravated after slight exertion. □3: Spontaneous sweating even at rest, and profuse sweating on exertion, like being drenched.
	Complexion	□0: None of the above symptoms □1: Dull complexion without lustre □2: Sallow and dull complexion □3: Purplish-dark complexion
	Lip colour	□0: None of the above symptoms □1: Slightly dark lips □2: Purplish-dark lips □3: Purplish-black lips
	Tongue body	□0: None of the above symptoms □1: Pale and dark tongue body □2: Purplish tongue body □3: Purplish tongue body with scattered ecchymoses and petechiae, or tortuous and cyanotic sublingual veins
	Pulse condition	□0: None of the above symptoms □2: Deep and thready pulse, or feeble and forceless pulse

### Exclusion criteria

2.4

A diagnosis of hypertrophic obstructive cardiomyopathy (HOCM), cardiac amyloidosis, hemochromatosis, Fabry disease, stress (Takotsubo) cardiomyopathy, constrictive pericarditis, muscular dystrophy, severe valvular heart disease, or Unstable coronary artery disease.A diagnosis of stroke or transient ischemic attack (TIA) within the past 3 months, or having undergone coronary artery bypass grafting (CABG), valve replacement surgery, or other major cardiovascular surgery within the past 3 months.Inability to exercise due to lung disease [e.g., forced expiratory volume in 1 s (FEV1) <50% of predicted value, or COPD GOLD stage III–IV], or any condition that may interfere with cardiopulmonary exercise testing.Pregnancy, current breastfeeding, or planning to become pregnant during the study period.Any serious illness that may affect the subject's clinical course, such as: Acute exacerbation of chronic obstructive pulmonary disease (COPD); Acute or chronic liver disease [alanine aminotransferase (ALT) ≥3× the upper limit of normal (ULN)]; Severe renal impairment [defined as serum creatinine (Cr) ≥3 mg/dL, estimated glomerular filtration rate (eGFR) ≤30 mL/min/1.73 m^2^, or receiving regular dialysis]; Anemia [hemoglobin (Hb) <90 g/L]; Gastrointestinal surgery or disease that may affect the absorption of the investigational drug; Acute or chronic pancreatitis; Severe primary hematologic or psychiatric disorders; Any documented active or suspected malignancy, or history of malignancy, within 1 year prior to screening.Any disease (other than heart failure) that, in the investigator's judgment, is associated with a life expectancy of less than 6 months.Known history of allergies, including allergies to multiple drugs or foods, or known allergy to any component of Shengxian Yixin Granule.Inability to exercise, or conditions that, in the investigator's judgment, may affect exercise, inability to perform activities of daily living, or inability to take oral medications.Use of herbal medicines with similar therapeutic effects (e.g., decoctions, patent herbal medicines, or herbal injections) within the past 7 days.Receipt of any investigational therapy other than the study drug.Suspected or documented history of alcohol or drug abuse.Inability to comply with the study assessment schedule for follow-up visits, or judged by the investigator to be unsuitable for continued participation in the trial.

### Withdrawal criteria and management

2.5

Regardless of the time or reason for withdrawal, any participant who does not complete the full course of the trial is considered a dropout. The investigator must document the reason for withdrawal in the case report form (CRF). The investigator should make every effort to contact the patient, complete as many of the scheduled assessments as possible, fill in the end-of-treatment follow-up record form, and document the time of the last dose whenever possible. For withdrawals due to adverse events, if after follow-up the event is ultimately judged to be related to the investigational drug, this must be documented in the CRF, the sponsor must be notified, and the event should be reported to the ethics committee as required.

### Discontinuation criteria

2.6

(1) The subject is judged by the principal investigator to be unsuitable to continue in the trial; (2) a serious adverse event directly related to the study treatment occurs, prompting immediate discontinuation of the study treatment; (3) the patient has poor compliance and is unable to complete the treatment or efficacy assessments in accordance with the study protocol.

### Termination criteria

2.7

(1) A major flaw in the trial protocol is identified during the trial, or significant deviations occur in its implementation; (2) the sponsor requests termination (e.g., due to funding issues, administrative reasons, etc.); (3) the regulatory authority requires termination.

### Laboratory thresholds and adverse event management measures

2.8

Laboratory abnormalities will be graded and recorded according to the Common Terminology Criteria for Adverse Events (CTCAE), Version 6.0, published by the US National Cancer Institute (NCI) (26). Any adverse events occurring during the trial, including subjective discomfort of subjects and laboratory test abnormalities, must be taken seriously, carefully analysed, and managed promptly to ensure subject safety. Should adverse events such as hepatic or renal dysfunction, bleeding risk, drug or food allergy, or gastrointestinal discomfort arise during the trial, appropriate measures—including symptomatic treatment, dose adjustment, treatment discontinuation, or observation—may be taken depending on the nature and severity of the event. Investigators are required to follow up all adverse events until they resolve to baseline, are assessed by the investigator as stable, or the subject is lost to follow-up or withdraws informed consent. All adverse events should be documented in the source medical records and the adverse event pages of the CRF to facilitate source data verification.

### Serious adverse event reporting procedure

2.9

Any serious adverse event occurring during the trial must be reported immediately to the principal investigator, the institutional drug clinical trial office, the ethics committee, and the project team, with the completion of a “Serious Adverse Event Report Form”, while simultaneously notifying the other investigators involved in the trial.

### Randomization and blinding

2.10

#### Randomization

2.10.1

This study uses the central randomization system (Interactive Web Response System, IWRS) of The First Affiliated Hospital of Henan University of Chinese Medicine, employing stratified block randomization for enrollment. The study will be conducted at four TCM hospitals. Using study site as the stratification factor, patients will be randomly assigned in a 1:1 ratio to either the SXYX group or the placebo group (74 patients per group). The randomization list was generated by an independent statistician using the IWRS, producing randomization sequence numbers from 001 to 148, ensuring balanced sample sizes within each stratum. Randomization assignment will be implemented and managed using the EDC system (Electronic Data Capture) of the Evidence-Based Medicine Center of The First Affiliated Hospital of Henan University of Chinese Medicine. Investigators will obtain the investigational drug numbers for enrolled patients through this system. The IWRS is integrated with the EDC system in real time. The system automatically conceals the unallocated randomization sequence from the assignment results, thereby achieving allocation concealment.

#### Blinding

2.10.2

Blinding Design: The randomization code list will be generated by the EDC system. Before the start of the clinical trial, an independent statistician will label the investigational drugs according to the drug numbers in the blinding list.Routine Unblinding and Emergency Unblinding: After the completion of the study, unblinding can be performed in the system, and the blinding list will be exported and provided to the statistical analysts for analysis. Emergency unblinding is required under the following conditions: (i) occurrence of a serious adverse event (SAE); (ii) occurrence of a serious complication; (iii) worsening of symptoms requiring emergency intervention. When emergency unblinding is deemed necessary, it should be performed after obtaining written approval from the site principal investigator, who will then log into the IWRS to perform the emergency unblinding. The lead hospital must be notified within 24 h after unblinding. Participants who withdraw from the trial due to perceived lack of efficacy must not be unblinded.Recording and handling of unblinding events: All unblinding events will be documented in detail, reported by treatment group, and reviewed periodically by the Data Safety Monitoring Board (DSMB). A formal assessment of blind integrity will be triggered only if the unblinding rate is unusually elevated or if there is a marked imbalance in the distribution of unblinding events between groups. Emergency unblinding events will be explicitly handled as “intercurrent events” within the framework of ICH E9(R1) (27), and multiple strategies will be employed in sensitivity analyses to evaluate their impact on the robustness of the conclusions.Responsibilities of the independent statistician, the Interactive Web Response System (IWRS), and the Electronic Data Capture (EDC) system: Independent statistician (not involved in clinical efficacy assessments): (i) generates the random allocation sequence and maintains the complete randomisation schedule; (ii) performs unblinding only after database lock at study completion or following an authorised emergency unblinding review by the DSMB; (iii) is not involved in patient enrolment, efficacy evaluation, or safety adjudication. IWRS (Interactive Web Response System): (i) implements central randomisation to ensure allocation concealment; (ii) allows emergency unblinding requests via the system in urgent situations (requiring dual authorisation: request by the investigator and approval by the independent unblinding reviewer); (iii) maintains an audit trail for all randomisation operations. EDC (Electronic Data Capture): (i) collects all clinical efficacy and safety data; (ii) does not store any treatment allocation information within the EDC system, thereby ensuring that data entry personnel, clinical coordinators, and data managers remain blinded; (iii) treatment assignment codes are only imported by the independent statistician for analysis after database lock.

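### The emergency unblinding rule is stated both as obligatory and as discretionary, with conflicting approval routes and conflicting statements on where the code list is generated and held

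*Protocol article*

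**What the plan says.** All the relevant text is in Sections 2.10.1 (Randomization) and 2.10.2 (Blinding) of the protocol article.

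**Trigger.** Section 2.10.2 says "Emergency unblinding is required under the following conditions: (i) occurrence of a serious adverse event (SAE", and then lists "ii) occurrence of a serious complication; (iii) worsening of symptoms requiring emergency intervention". The sentence that follows is conditional: "When emergency unblinding is deemed necessary, it should be performed after obtaining written approval from the site principal investigator".

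**Approval and execution.** The same section gives these arrangements:

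- The code is opened after "written approval from the site principal investigator, who will then log into the IWRS to perform the emergency unblinding".
- Under the duties of the IWRS, a request is described as "requiring dual authorisation: request by the investigator and approval by the independent unblinding reviewer".
- Under the duties of the independent statistician, unblinding is allowed after database lock or "following an authorised emergency unblinding review by the DSMB".

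**Code list.** Section 2.10.1 has the independent statistician generate the list with the IWRS, and then says "Randomization assignment will be implemented and managed using the EDC system". Section 2.10.2 opens by having the EDC generate the code list. It later gives that task back to the statistician and says that the EDC "does not store any treatment allocation information within the EDC system".

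**The concern.** An investigator who reads the first sentence literally would open the code for every serious adverse event, related or not, and whether or not the allocation would change anything for the patient. Such events are to be expected in a heart failure population. The person who opens the code in the first route is the site principal investigator, whose approval Section 2.11.3.1 also requires before any new core heart failure drug is started.

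The blind would then be lost selectively, in the patients who do worst. Their remaining assessments are peak VO2, 6-minute walk, NYHA class, EQ-5D and the TCM syndrome score, all of which depend on effort or judgement. A blind that has been broken cannot be restored at the analysis stage.

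The two other conflicts are practical. IWRS permissions cannot be configured from text that names two different approvers. The statement that data managers stay blinded rests on the EDC holding no allocations, which is hard to square with the EDC generating the list.

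**Working it through.** The protocol gives no expected rate of serious adverse events or of unblinding, so there is no figure of its own to reproduce. The check is mainly a comparison of sentences.

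**1. Trigger.** The first sentence makes unblinding obligatory on any of three events and sets no condition about relatedness or need. The second presupposes that someone decides whether unblinding is necessary. If the first governs, there is nothing to decide. If the second governs, the three events are only occasions to consider it. Section 2.9, the reporting procedure for serious adverse events, contains no unblinding step and so does not settle which governs.

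**2. Approval.**

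| Where in Section 2.10.2 | Who approves | Who opens the code |
|---|---|---|
| Routine and emergency unblinding | site principal investigator | site principal investigator, in the IWRS |
| Duties of the IWRS | independent unblinding reviewer, on the investigator's request | not stated |
| Duties of the independent statistician | DSMB review | independent statistician |

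The first two rows clash directly: approval either stays within the site or requires someone independent. The third row can be read as a separate limit on what the statistician may do, so it is an ambiguity rather than a certain third route.

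**3. Code list.** Two sources are named for the list: the statistician using the IWRS, and the EDC. The second cannot easily stand beside the statement that the EDC stores no allocation. The sentence on managing assignment through the EDC is a weaker conflict, because investigators obtain drug numbers there and a drug number need not disclose the arm.

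**4. Path into the primary result.** Section 2.18 makes the mITT set the primary analysis set: randomised, at least one dose, at least one post-baseline primary assessment. Nothing in that definition removes an unblinded patient. Section 2.17 expressly keeps patients with rescue therapy or with hospitalisation for any reason. A patient whose code is opened before week 12 or between weeks 12 and 24 can therefore contribute later peak VO2 values to the primary model, measured after the site investigator knows the arm.

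**5. Size, as illustration only.** Number of codes opened = assumed share of patients with a triggering event × 148.

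- 5%: 0.05 × 148 = 7.4, about 7
- 10%: 0.10 × 148 = 14.8, about 15
- 25%: 0.25 × 148 = 37

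The shares are assumptions; 148 is the planned enrolment in Section 2.2.

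**The case against.** **Discretion is implied.** The conditional sentence, the written approval and the language of requests all suggest case-by-case judgement. This stands: a reader might infer that unblinding is mandatory for every serious adverse event, and the document does not support that without qualification. What it supports is a contradiction, and a site could reasonably act on either half.

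**Safeguards exist.** Section 2.10.2 provides for documentation by group, periodic DSMB review, treatment of emergency unblinding as an intercurrent event with several sensitivity strategies, and no unblinding for perceived lack of efficacy. Section 2.14.1.1 sets objective criteria for maximal effort and blinded central adjudication of a 10% sample of exercise tests. These deserve credit, but the unblinding provisions act after the code is open, and the adjudication covers one test in ten. The formal check of blind integrity starts only if the unblinding rate is unusually high or markedly unbalanced. If every serious adverse event opened a code, a high rate would be built in and might not look unusual.

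**Inference about other patients.** A reader might infer that opened codes reveal the rest of a randomisation block. The document does not support this. It gives no block size, does not say that sites know it, and has labels show only a drug number. Section 2.11.3.1 also adds SGLT2 inhibitor use as a stratification factor, which would divide each site's sequence. Suppose nevertheless that block size and boundaries were known and each code was opened independently with probability p. In a block of size b, a blinded patient's arm is certain only if all b/2 patients of the other arm are opened, with probability p^(b/2). For b = 4 this is 0.05² = 0.25% to 0.25² = 6.25%. A guess better than even would be possible with probability 1 − [(1 − p)³ + 2p²(1 − p)], that is 14% at p = 0.05 and 48% at p = 0.25. This is a conditional risk, and the point does not rest on it.

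**Event rate.** A reader might take the readmission and mortality figures in the Introduction as support for a high rate. They describe HFpEF in general. This trial takes stable NYHA II–III patients aged up to 75 with no acute heart failure admission in the preceding 4 weeks, and patients who die have no later assessments to bias.

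**Conclusion.** The point holds as an internal contradiction with a real but unquantified risk to the blind. Three things need reconciling: whether the listed events oblige unblinding or only permit it; whether approval lies with the site principal investigator or an independent reviewer, and how the DSMB review relates to either; and which system generates and holds the code list.

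Under the literal reading, the loss of blinding falls on patients with the worst courses, who remain in the primary analysis set. That consequence follows from the text. Its extent does not: 7 to 37 opened codes is what an assumed 5–25% of 148 would give, and the true figure depends on an event rate that the protocol does not state and on which sentence sites follow. The conclusion needs no assumption about block size or background mortality.

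**What to change.** - **Trigger:** reconcile the obligatory and the conditional sentence, so that a serious adverse event does not by itself automatically open the code. The clinical judgement of when a participant's allocation is needed remains with the investigators.
- **Approval:** state one authorisation route, check that it can be followed in an emergency, say whether the DSMB clause applies only to the statistician, and configure IWRS permissions to match.
- **Disclosure:** restrict the revealed allocation to those who need it for that participant.
- **Code list:** correct the sentences in Sections 2.10.1 and 2.10.2 so that the list has one stated origin and is held only in the IWRS and by the independent statistician. Describe the EDC as handling drug numbers without allocations, if that is the intention.

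The cost is revised wording in two sections, a change of IWRS permissions and a note to the four sites. It needs no additional patients, visits, assessors or procedures, and the sample size is unaffected. It should be in place before codes can be opened at the sites.
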